## Abstract

**Background:**

Real-time functional magnetic resonance imaging (rtfMRI) is used for neurofeedback training (NFT). Preliminary results suggest that it can help patients to control their symptoms. This study uses rtfMRI NFT for relapse prevention in alcohol dependence.

**Methods/design:**

Participants are alcohol-dependent patients who have completed a detoxification programme within the past 6 months and have remained abstinent. Potential participants are screened for eligibility, and those who are eligible are randomly assigned to the treatment group (receiving rtfMRI NFT in addition to treatment as usual) or the control group (receiving only treatment as usual). Participants in both groups are administered baseline assessments to measure their alcohol consumption and severity of dependence and a variety of psychological and behavioural characteristics that are hypothesised to predict success with rtfMRI NFT. During the following 4 months, experimental participants are given six NFT sessions, and before and after each session various alcohol-related measures are taken. Participants in the control group are given the same measures to coincide with their timing in the experimental group. Eight and 12 months after the baseline assessment, both groups are followed up with a battery of measures. The primary research questions are whether NFT can be used to teach participants to down-regulate their brain activation in the presence of alcohol stimuli or to up-regulate their brain activation in response to pictures related to healthy goal pursuits, and, if so, whether this translates into reductions in alcohol consumption. The primary outcome measures will be those derived from the functional brain imaging data. We are interested in *improvements* (i.e., reductions) in participants’ alcohol consumption from pretreatment levels, as indicated by three continuous variables, not simply whether or not the person has remained abstinent. The indices of interest are *percentage of days abstinent*, *drinks per drinking day*, and *percentage of days of heavy drinking*. General linear models will be used to compare the NFT group and the control group on these measures.

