**Fig. 1 Fig1:**
[figure not shown]
Consolidated Standards of Reporting Trials (CONSORT) flow diagram of the phases of the BRAINTRAIN trial

**Table 1 Tab1:** Standard Protocol Items: Recommendations for Interventional Trials (SPIRIT) diagram

	Study period					
	Enrolment	Allocation				
Timepoint	Pre intervention	Time 0	Baseline	Post intervention	8-month follow-up	12-month follow-up
Enrolment:						
Eligibility screen	X					
Informed consent	X					
Allocation		X				
Interventions:						
rtfMRI NFT + TAU				X		
TAU				X		
Assessments:						
Alcohol Timeline Followback	X		X	X	X	X
Drinking Urges Questionnaire			X	X	X	X
Obsessive Compulsive Drinking Scale			X	X	X	X
Alcohol Stroop Test			X	X	X	X
Severity of Alcohol Dependence			X			
Thought Control Questionnaire			X			
Thought Control Ability Questionnaire			X			
Profile of Mood States			X		X	X
Hospital Anxiety and Depression Scale			X	X	X	X
Beck Depression Inventory			X	X	X	X

*rtfMRI* real-time functional magnetic resonance imaging, *TAU* treatment as usual

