### Baseline assessment

During the baseline assessment, participants complete the following instruments: a demographic questionnaire (which asks about participants’ age, gender, level of education, and socioeconomic status); a National Health Service (NHS) resources utilisation questionnaire (which asks about the use of prescription medications and treatment services); and various standardised measures which are shown in Table 2. Patients are randomised after the baseline session.

**Table 2 Tab2:** Standardised measures administered

Measure	Description
Alcohol Timeline Followback (TLFB) Questionnaire [13]; primary outcome measure	Measures alcohol use during the 4 months immediately prior to patients’ entering treatment
Drinking Urges Questionnaire [22]; secondary outcome measure	Assesses participants’ desire to drink, expectations of positive effects following drinking, relief of withdrawal and negative affect following drinking, and intentions to drink
Obsessive Compulsive Drinking Scale (OCDS) [23]; secondary outcome measure	Measures respondents’ obsessive thoughts about alcohol use and compulsive behaviours related to drinking
Alcohol Stroop Test [24]; secondary outcome measure	Measures alcohol-related attentional distraction by alcohol-related stimuli
Severity of Alcohol Dependence Questionnaire [25]; primary outcome measure	Measures the degree to which patients are physically and psychologically dependent on alcohol
Thought Control Questionnaire (TCQ) [26]; BRAINTRAIN core outcome measure	Assesses the effectiveness of strategies used to control unpleasant or unwanted thoughts
Thought Control Ability Questionnaire (TCAQ) [27]; BRAINTRAIN core outcome measure	Measures individuals’ perceived ability to control unwanted and intrusive thoughts
Profile of Mood States (POMS) [28]; BRAINTRAIN core outcome measure	Measures anger, confusion, depression, fatigue, tension, and vigour
Hospital Anxiety and Depression Scale (HADS) [29]; BRAINTRAIN core outcome measure	Measure anxiety and depression
Beck Depression Inventory (BDI) [30]; BRAINTRAIN core outcome measure	Measures depression

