While in the scanner, participants in the experimental group are again exposed to alcohol-related stimuli, such as pictures of alcoholic drinks, and they are trained to regulate their responses in specific brain regions that are activated by the stimuli. In addition, participants are exposed to pictures showing alternative, socially desirable goals, such as family/relationships or employment. The rationale for including the two categories of stimuli is that we earlier demonstrated at a neural level that heavy drinking is associated with overvaluation of alcohol and undervaluation of alternative, socially desirable goals [14]. Moreover, consistent with motivational theory [15–17], it has been shown that problem drinkers’ success in reducing their drinking is associated with the degree to which they have other satisfying alternative goals to pursue and enjoy [16].

The size of the images that participants see corresponds to the level of activation. They are told to use any kind of mental strategy at their disposal (e.g. thinking about the negative consequences of drinking) that helps to reduce size of the image (in the case of alcohol pictures) or increase size of the image and thereby the degree of brain activation (in the case of healthy, goal-related pictures).

Experimental participants have six NFT training sessions spread across 4 months, and they are also asked to practice at home the mental strategies they used in the MRI scanner. They also (1) rate their urges to drink before, during, and after each training session, and (2) complete questionnaires and other tests to measure their alcohol consumption and other relevant aspects of their behaviour. Control participants complete the same measures that are timed to coincide with their administration to the experimental group. The primary outcome measures are obtained 4 months after the baseline assessment. Eight and 12 months after baseline assessment both groups complete a follow-up assessment battery.

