A moving average filtre of four volumes is used to overcome spikes and signal drops and to avoid large fluctuations in the size of the pictures. The percentage signal change is calculated using this equation:$$ fb = \left( val-bl\right)/bl\ast 100 $$

The percentage signal change (PSC) is then normalised to a value between −1 and +1 by dividing the *fb* value by a predefined maximum PSC of 1 %. This is done in order to be able to resize the pictures in the predefined way.

Between the *f*MRI runs, the experimenter speaks to the participant using an intercom and gives the participant the opportunity to rest. Participants in the control group are invited to attend four behavioural assessment sessions (baseline assessment, primary assessment after 4 months, and a follow-up assessment after 8 and 12 months).

All adverse events and serious adverse events (SAEs) will be recorded on the appropriate Case Report Form. Events meeting the criteria for a SAE will be reported according to the timelines specified in the study protocol (e.g. an SAE form should be completed for all SAEs within 24 h).

Post trial, all participants will remain under the care of their primary treating physician. Cardiff University will provide indemnity and compensation in the event of a claim by a participant, or by someone on a participant’s behalf, for negligent harm as a result of the study design and/or in respect of the protocol authors/research team. Cardiff University does not provide compensation for non-negligent harm.

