The behavioural data will be analysed using SPSS or another appropriate statistical software package. The primary analyses will compare the experimental and control groups on three drinking indices (percentage of days abstinent, drinks per drinking day, and percentage of days of heavy drinking) at the primary endpoint (4 months after the baseline assessment). For these analyses, a general linear model will be used. Covariates will include potential variables that determine participants’ success with the NFT (e.g. their age and gender and drinking indices at baseline) and the variables that were used to balance the two groups during randomisation. Effect sizes for the intervention will be evaluated using confidence intervals around the group difference. Analyses will be conducted separately for the follow-up assessments, again using general linear models adjusted for baseline covariates and randomisation variables. Outcome measures related to craving will be evaluated for both immediate and sustained effects of the NFT.

In exploratory analyses, data from the homework diaries will be examined for a potential relationship between the amount of self-regulation practice that participants report and their scores on craving and alcohol consumption. Finally, the relationship between nonalcohol-related measures (e.g. thought control ability, intellectual ability) and the alcohol-related outcome measures will be examined using analysis of covariance (ANCOVA) or correlational and regression analyses. Nonspecific effects of the NFT on participants’ mood will be examined using the measures related to emotional processes (e.g. the POMS).

A publication policy will be developed and reviewed during the course of the trial, which will include details of dissemination plans to health care professionals. Publications from the BRAINTRAIN consortium will be coordinated by the Executive Committee of BRAINTRAIN (chaired by the PI) in collaboration with the funding organisation. The trial results will be submitted for publication in an online open access journal.

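### Primary status is given to imaging measures, to three drinking indices and to a baseline-only dependence scale, with no rule linking them

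*Protocol article*

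**What the plan says.** Primary status is assigned in three places in the protocol article.

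- Abstract, Methods/design: "The primary outcome measures will be those derived from the functional brain imaging data". The same paragraph then describes the three drinking indices as the indices of interest and says the groups will be compared on them.
- Analyses: "The primary analyses will compare the experimental and control groups on three drinking indices", at a primary endpoint 4 months after baseline, by general linear model.
- Baseline assessment, Table 2: "Alcohol Timeline Followback (TLFB) Questionnaire [13]; primary outcome measure", and also "Severity of Alcohol Dependence Questionnaire [25]; primary outcome measure". Imaging is not in this table.

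On timing, the Intervention section says: "The primary outcome measures are obtained 4 months after the baseline assessment". In Table 1 the row "Severity of Alcohol Dependence" has one mark, under baseline.

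On who is scanned, the Intervention section says: "While in the scanner, participants in the experimental group are again exposed to alcohol-related stimuli". For controls it says: "Participants in the control group are invited to attend four behavioural assessment sessions", one of which is called the primary assessment, at 4 months.

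The Sample size estimation section gives power for 20 evaluable participants per group at a 0.05 significance level: an effect of 0.8 with 70% power, up to 1.1 with 90%. It does not name the outcome.

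**The concern.** The labels lead to different headline results. A reader following the abstract would judge the trial on brain activation; a reader following Analyses would judge it on drinking. The two can disagree. If trained participants regulate the target area but the arms drink alike, the abstract supports saying that the primary outcome was met and Analyses supports the opposite. If drinking improves without measurable regulation, the positions reverse.

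The two outcomes also carry different kinds of evidence. The drinking comparison uses the randomisation. The imaging contrast does not, because only one arm contributes data. Power planned for two groups therefore says nothing about imaging, and an imaging result cannot by itself support a claim that adding NFT to usual treatment is better than usual treatment alone.

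**Working it through.** **1. The labels side by side**

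| Measure | Called primary in | Measured in | Available at 4 months? |
|---|---|---|---|
| Imaging | Abstract | NFT arm only | NFT arm, from the training sessions |
| Three drinking indices (from TLFB) | Analyses; TLFB in Table 2 | Both arms | Yes |
| SADQ | Table 2 | Both arms | No |

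**2. The SADQ.** Table 1 marks it at baseline only. It is not among the instruments listed under Assessment at NFT sessions, Four-month assessment of the control group, or Follow-up assessments. Primary outcomes are to be obtained at 4 months, and no SADQ value exists then or later. The label is impossible as scheduled.

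**3. The imaging contrast.** Analyses compares neurofeedback runs with mirror runs and examines change across sessions. Both are within trained participants. Mirror runs replay the same stimulus without attempted regulation, so there is a within-participant control but no between-arm comparison.

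**4. The stated power.** Inputs from Design and Sample size estimation: 25 + 25 = 50 randomised; 20% dropout, so 50 × (1 − 0.20) = 40, or 20 per group; significance level 0.05. The article does not say whether the test is one- or two-sided.

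For a two-sample t-test with n per group, the noncentrality is d × √(n/2) with 2n − 2 = 38 degrees of freedom.

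- d = 0.8: 0.8 × √10 = 2.53; two-sided power 69.3% (stated 70%).
- d = 1.1: 1.1 × √10 = 3.48; two-sided power 92.4% (stated 90%). Power of exactly 90% needs d = 1.05, which rounds to the stated 1.1.
- One-sided tests give 79.9% and 96.2%, which do not fit.

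The figures therefore reproduce as a two-sided, two-group comparison on a single outcome. Of the measures called primary, only the drinking indices are recorded in both arms at 4 months, so the calculation can apply only to one of them.

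**5. Three indices under one primary heading.** Assume that each is tested at two-sided 0.05 and that success on any one counts. The article states no such criterion, so this is an illustration.

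- Independent: 1 − 0.95³ = 14.3%.
- Assumed common correlation of 0.5, 0.8 or 0.9 (simulated normal test statistics): 12.5%, 9.8% or 8.4%.
- Adding one independent imaging test: 1 − 0.95⁴ = 18.5% if all are independent; 16.8% to 13.0% for index correlations of 0.5 to 0.9.

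If the 0.05 were split equally, 0.05/3 = 0.0167, power with 20 per group would be 51.6% at d = 0.8 and 83.0% at d = 1.1. The detectable effects would become 0.96 (70% power) and 1.21 (90% power).

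**The case against.** The best defence is that imaging and drinking are not rivals. The abstract poses a two-step question: can participants learn to regulate, and if so does drinking fall? Study objectives lists both as main aims and brings in the control group only for the second. The phrase about primary analyses in Analyses follows the sentence that introduces the behavioural data, so it may mean primary among the behavioural analyses. A target-engagement outcome is also defensible in an early-phase feasibility trial. This stands as far as it goes: imaging and drinking could be co-primary or sequential. But the article never says so, and it gives no rule for a split result.

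Three stronger readings are tempting and are not supported.

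- A reader might infer that the imaging outcome is uncontrolled. It is not: mirror runs are a genuine within-participant control, and the first aim asks only about trained participants. What is missing is a randomised comparison, and the article claims no between-arm imaging effect.
- A reader might infer that the result will be picked after the data are seen. Analyses fixes the indices, the time point and the model, and also the imaging contrast. A full protocol, analysis plan or registry record may settle the hierarchy. The contradictory text permits such a choice; it does not show one.
- A reader might infer that the imaging test is better powered. A between-person effect and a within-person effect are scaled by different standard deviations, and the article assumes no imaging effect size, so the comparison would not be like for like.

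The SADQ label may be a slip in the table: the abstract treats severity of dependence as a baseline characteristic, and no analysis uses it as an outcome. It is still an error, but not another route to a positive claim.

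**Conclusion.** The point holds as an internal contradiction that needs correcting. Primary status is assigned inconsistently, and no ranking, co-primary rule or decision rule reconciles the places. The SADQ label is wrong on the article's own schedule. The imaging outcome can answer the first aim but cannot carry an efficacy claim, and the power statement, though correct, cannot describe it.

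The main consequence is qualitative: following the abstract or Analyses could give opposite conclusions from the same data. The numerical part is secondary. A family-wise error of up to about 14% for the three indices rests on an assumed any-one-succeeds criterion at 0.05 and on independence; it falls to 8.4% at an assumed correlation of 0.9. The feasibility label softens that multiplicity concern but leaves the contradiction in place. A multiplicity rule may be in a plan not shown, so its absence from the article is not the fault. It matters here because any repair that only makes drinking primary still leaves three candidates.

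**What to change.** State one rule, in the same terms, in the abstract, Table 2 and Analyses. Either of these would do:

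1. Make the 4-month between-arm drinking comparison primary, with imaging self-regulation (NFT minus mirror runs) as a mechanistic outcome in the NFT arm only. This fits the Intervention, Sample size estimation and Analyses sections as they stand.
2. Declare an explicit sequential or co-primary rule covering imaging and drinking, and say that only the between-arm drinking comparison supports an efficacy claim.

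Under either option:

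- name one of the three drinking indices as primary, or state the multiplicity rule for all three;
- relabel the SADQ in Table 2 as a baseline measure or covariate;
- say in Sample size estimation that the power refers to the between-arm drinking comparison.

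The cost is wording in the article and in the matching full protocol or analysis plan. No new data or visits are needed. Naming one index leaves the stated power as it is. An equal split of the 0.05 over three indices would raise the detectable effects to the 0.96 and 1.21 shown above, and the power statement would then have to be revised.

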**Discussion:**

Relapse in alcohol dependence is a recurring problem, and the present evaluation of the role of rtfMRI in its treatment holds promise for identifying a way to prevent relapse.

**Trial registration:**

ClinicalTrials.gov Identifier: NCT02486900, registered on 26 June 2015.

**Electronic supplementary material:**

The online version of this article (doi:10.1186/s13063-016-1607-7) contains supplementary material, which is available to authorized users.

## Background

There has been a longstanding interest in the use of biofeedback in the treatment of a variety of medical and psychiatric disorders. The basic principle of biofeedback is that if patients are provided with feedback about the normally involuntary and uncontrollable physiological responses associated with their illness, they can use mental strategies to control these responses and thereby improve their symptoms [1].

During the 1970s, there was a surge of interest in biofeedback using electroencephalography (EEG) Clinical syndromes for which it was attempted included tension headache, hypertension, chronic anxiety, and eating disorders. Although promising results were obtained, certain methodological problems prevailed, especially small sample sizes and the absence of satisfactory control conditions [2]. Thus, definitive conclusions about the efficacy of biofeedback could not be reached. Nevertheless, the interest in it prevailed into the 1980s and beyond, and at this time there was an increase in the number of ailments for which it was used. Additionally, EEG biofeedback was extended to cognitive enhancement and skill training for musicians and dancers and even surgeons, again with promising results. Today various kinds of biofeedback are being offered in certain countries for a variety of clinical problems, including addiction, anxiety, attention deficit/hyperactivity disorder (ADHD), depression, epilepsy, asthma, and chronic pain [3].

In the past decade, there has been a revival of scientific interest in biofeedback and its clinical applications, partly driven by the development of real-time functional magnetic resonance imaging (rtfMRI) neurofeedback training (NFT). For NFT, rtfMRI has advantages over EEG. For example, it localises brain signals to specific areas of the brain with more precise resolution, and it capitalises on the fact that relevant brain areas can be activated when patients only imagine particular events happening (e.g. moving a limb of the body, having a drink of alcohol). rtfMRI NFT has already been used in pilot studies to help patients with a variety of disorders to ameliorate their symptoms or unwanted behaviour. These include patients with debilitating pain [4], Parkinson’s disease [5], depression [6], and nicotine addiction, or alcohol [7–10]. The feedback that patients receive about their brain reactions and their ability to regulate them seems to have an added benefit in that it helps them to acquire a sense of control over their symptoms (e.g. [8]). Despite these promising initial results, additional research is needed to identify (1) variables that determine the effectiveness of rtfMRI NFT, and (2) optimal strategies for using it in clinical applications.

### BRAINTRAIN: taking imaging into the therapeutic domain

BRAINTRAIN (http://www.braintrainproject.eu/) is a research project supported by the European Commission under the Health Cooperation Work Programme of the 7th Framework Programme that is seeking to achieve these goals. BRAINTRAIN, coordinated by coauthor DL at Cardiff University, is a 4-year project to (1) further test whether rtfMRI is an effective additional form of treatment for people suffering from a variety of mental and behavioural disorders, and (2) identify variables that determine the effectiveness of rtfMRI NFT. The disorders that are being investigated include autism spectrum disorder (Universidade de Coimbra, Portugal), alcohol dependence (Cardiff University), posttraumatic stress disorder (Tel Aviv University, Israel), binge-eating disorder (Eberhard Karls Universität Tübingen, Germany), and childhood anxiety (University of Oxford/King’s College London).

The purpose of the present article is to describe the component of this research programme that is being conducted at Cardiff University. It is an early phase randomised feasibility trial to assess the effectiveness of rtfMRI NFT in the treatment of alcohol dependence.

